Participants (adolescents with depressive symptoms) are recruited by the ACDC trainers (both intervention and “active control” ones), and they are offering their own courses by placing information on schools and health centers, providing information through GPs, advertisements in local newspapers, on websites for youth, information on the local hospital’s medical meetings. Participants are recruited by either themselves take direct contact with course retainers, or they are referred by health visitors, GPs, psychiatric clinics, municipal services, school counselors, and the like. It will be established with doctor/referring in terms of differential diagnosis and considering further action after the course if necessary.

Fifteen course leaders for the intervention group received their training for a full week in October 2015, while the 15 leaders of “practice as usual” received a one-day training in how to recruit adolescents in October. Adolescents have been recruited throughout November and December 2015. Following a screening interview, baseline measures of all study measures was administered (see Table 2). The trial of the first cohort started in January 2016 and ran for 14 weeks, either by 10 sessions of the ACDC (treatment condition) or “practice as usual” for the control condition. Two weeks before the trial, the main outcome measure of depression was assessed. In addition to post-test in spring 2016, we will collect 6- and 12- month follow-ups. Personal number will be kept for five years in order to collect relevant information from public registers to further examine dropout.

**Table 2 Tab2:** Measures to be administered at each measurement occasion

Measure/Scale	References	S	T0	T1	T2	T3	T4
Beck Depression Inventory	Beck et al. 1961 [42]	X					
Demographics			X				
Center for Epidemiologic Studies Depression Scale (CES-D)	Radloff, 1977 [44]		X	X	X	X	X
Dysfunctional Attitudes Scale (DAS)	De Graaf et al., 2009 [53]		X		X	X	X
Ruminative Response Scale (RRS)	Nolen-Hoeksema & Morrow, 1991; Treynor et al., 2003 [55, 56]		X		X	X	X
Automatic Thoughts Questionnaire (ATQ)	Hollon & Kendall, 1980; Netemeyer et al. 2002 [51, 52]		X		X	X	X
Emotion Regulation Questionnaire (ERQ)	Gross & John, 2003 [58]		X		X	X	X
Hopkins Symptom Checklist (SCL-10) anxiety items	Strand et al., 2009 [49]		X		X	X	X
Aggression	Roland & Idsøe, 2001 [50]		X		X	X	X
Intentions to quit school	Studsrød & Bru, 2009 [48]		X	X	X	X	X

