### Sample size and power calculations

Because the design is a single-centre cluster-randomized effectiveness trial with active control, where groups rather than individuals are randomized, possible cluster effects must be accounted for when calculating appropriate sample size [61]. We approximated cluster effects influencing our main outcome (depressive symptoms) by taking advantage of data from the existent study on ACDC [37], and calculated intraclass correlations (ICC’s) with the course groups as cluster. ICC for depressive symptoms was .08. Our calculations showed that with a .05 level of significance, power = .80, ICC = .08, number of clusters = 25, cluster size = 8, *N* = 200, we may be able to detect effect sizes of .49 (about medium effects according to (Cohen, 1988). We recruited 30 course leaders rather than 25 and we can withstand a total waiver of five of the groups while still identifying the effect size we have calculated.

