### Statistical analysis

SPSS will be used for 1) descriptive analyses for each time point and 2) repeated measures General linear models (GLM) for estimation of intervention effects. Structural equation modelling (SEM) will be used for latent growth curve models (LGC) to investigate individual variations in level and change across time [62–64]. The LGC can be used for estimation of intervention effects by comparing intervention and control group data through multiple-group LGC. These results can be compared with results from GLM. The LGC can also be expanded to Latent growth mixture models to explore whether there are sub-groups of individuals constituting specific clusters with change patterns deviating from the average change pattern estimated by use of traditional LGC [65]. Predictors can be added to the trajectories. Missing data will be handled by the FIML procedure in Mplus (if MAR).

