### Study status

The intervention started in January 2016. Out of a total of 30 recruited course-leaders, only 19 was established due to difficulties in the recruitment process, and some with low cluster size. In order to fulfill the requirements following our power-calculations, more adolescents need to be recruited. Another training of course leaders will take place in the autumn of 2016, so that an additional intervention period can be executed. Recruitment procedures will be revised. The planned additional intervention will take place in the spring of 2017.

For the intervention in the spring of 2016, post-test assessments are scheduled to be completed by the end of June 2016.

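### CES-D is measured twice before treatment, but the analysis section gives these waves no baseline role and names no T2 contrast; baseline adjustment would be a nearly free improvement

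*Protocol article*

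**What the plan says.** The Design section sets five assessments: T0 and T1 before the course, T2 after it, and T3 and T4 at 6 and 12 months. On the second pre-treatment CES-D it says: "Two weeks before the trial, the main outcome measure of depression was assessed". Table 2 confirms CES-D at all five waves. Table 1 lists the pre-test and T1 next to T2, T3 and T4 as occasions of CES-D as a primary outcome.

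The Statistical analysis section assigns estimation of intervention effects to repeated-measures GLM in SPSS. It adds "latent growth curve models (LGC) to investigate individual variations in level and change across time", and says that a multiple-group version can also estimate the effect and be compared with the GLM result. Predictors of the trajectories are mentioned as a possibility, and none is named. The section does not give CES-D at T0 or T1 a role as covariate, name the contrast that is the T2 effect, or give the shape of the growth curve.

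The Sample size section states: "Our calculations showed that with a .05 level of significance, power = .80, ICC = .08, number of clusters = 25, cluster size = 8", and on that basis "we may be able to detect effect sizes of .49".

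**The concern.** Taken together, Table 1 and the analysis section suggest a model in which T0 and T1 are two of five levels of time. Three things could then go wrong.

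- A change contrast that leaves the arm means free before treatment is less precise than adjusting for the same two measurements.
- The GLM group main effect averages over two waves at which there can be no effect. The omnibus arm-by-time test has 5 - 1 = 4 degrees of freedom and is not the T2 difference.
- A straight growth line through all five waves lets the untreated T0-T1 segment help set the slope.

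Precision is scarce in this trial: the Study status section reports that only 19 of 30 groups were established, some of them small. Starting severity could also differ by arm, because leaders were allocated and trained before they recruited adolescents. A baseline-adjusted contrast uses data already scheduled and addresses part of both problems.

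**Working it through.** **Inputs.** From the Sample size section: alpha .05 (two-sided assumed), power .80, ICC .08, 25 clusters of 8, N = 200, SD taken as 1. Wave dates are from the note to Table 2. The correlation r of CES-D between waves is not given, so .3 to .7 is assumed. In steps 2 and 3 it is taken as equal for all pairs of waves and at both the individual and cluster level.

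**1. The plan's own figure.** Design effect = 1 + 7 × .08 = 1.56. SE = 2 × √(1.56/200) = .1766. Detectable effect = (1.960 + .842) × .1766 = .495, and power at .49 is .792. The stated .49 therefore reproduces as an unadjusted comparison at one time point. (With a t distribution on 23 df it is .517; the ratios below do not change.)

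**2. Change contrast against ANCOVA at T2.** Variance relative to the unadjusted T2 comparison:
- change from the T0/T1 mean: 1 + (1 + r)/2 - 2r = 1.5(1 - r)
- ANCOVA on T0 and T1: 1 - 2r²/(1 + r)

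The detectable effect is .495 × √(relative variance).

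| r | Change: variance | ANCOVA: variance | Ratio | Detectable effect: change | Detectable effect: ANCOVA |
|---|---|---|---|---|---|
| .3 | 1.050 | .862 | 1.22 | .507 | .459 |
| .5 | .750 | .667 | 1.125 | .429 | .404 |
| .7 | .450 | .424 | 1.06 | .332 | .322 |

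The change contrast therefore carries about 6% to 22% more variance. The excess depends on the correlation pattern. If correlation instead decays with time and is .5 between T1 and T2, the relative variances are 1.000 and .750, which is 33% more.

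**3. Keeping T0 and T1 as outcomes with arm means set equal there.** At r = .5 the variance of the T2 effect is .667, the same as ANCOVA. Using the waves as outcomes does not in itself lose precision; leaving their arm means free does.

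**4. Group main effect.** For true differences 0, 0, d, d, d over T0 to T4, the average is 3d/5 = 0.60d.

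**5. Straight-line growth.** Place the waves at 0, 1, 6.5, 12.5 and 18.5 months, an approximation to Table 2, with the same differences.
- Mean time 7.7; Sxx = 59.29 + 44.89 + 1.44 + 23.04 + 116.64 = 245.3; Sxy = -1.2 + 4.8 + 10.8 = 14.4.
- Slope = 14.4/245.3 = .0587; intercept = .6 - .0587 × 7.7 = .148.
- Fitted difference at T2: .148 + .0587 × 6.5 = 0.53d. At T4: .148 + .0587 × 18.5 = 1.23d.

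With waves at -1.5, 0, 5, 11 and 17 months the results are 0.52d and 1.23d. On those dates, with intercepts also held equal across arms (r = .5), T2 is about 0.40d. A piecewise curve, or a GLM contrast at T2 with time categorical, recovers d in full.

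**The case against.** The strongest objection is that the article never says which waves enter the models or in what role. Table 1 is a registry listing of assessment times, not a model specification, and the Design section itself treats the pretest data as baseline. A reader might infer that both waves definitely enter as free outcomes, so that precision is wasted and the T2 effect distorted. The text does not support that. Time in a repeated-measures GLM is categorical, so a T2 contrast is available within it, and nothing says the growth curve is linear. A condensed article may also leave such detail to an analysis plan. All of this stands, and it is why the losses above are conditional.

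Three further inferences should be resisted.

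- Regression to the mean after entry at BDI 10 or more applies to both arms and largely cancels between them.
- Adjustment does not correct imbalance from recruitment after allocation; it can only reduce the part carried by the measured baseline.
- The absence of a cohort term is not an error. The Study status section says "The planned additional intervention will take place in the spring of 2017", under revised recruitment procedures, but the article's silence on cohort may be filled elsewhere, and nothing shows that arm sizes differ between cohorts.

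What remains is that the analysis section does choose its effect estimators, and a better use of the two baselines is available within almost the same models.

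**Conclusion.** The point holds as a recommended improvement to the stated method, not as a demonstrated error. That CES-D is measured twice before treatment, and that both waves are listed as occasions of the primary outcome, is plain in the text. That they act as levels of time is an inference, so confidence in the harm is moderate.

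The precision gain over a change from the T0/T1 mean is modest. At an assumed r of .5 the change contrast has 12.5% more variance than ANCOVA. The gain rests on assumed correlations throughout. The larger figures (0.60d for the group main effect; 0.53d at T2 and 1.23d at T4 for a straight line) apply only if those particular summaries are used and the effect is constant from T2 to T4.

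**What to change.** In the Statistical analysis section:

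- Model CES-D at T2, T3 and T4 as outcomes, with CES-D at T0 and T1 as covariates. Alternatively, keep T0 and T1 as outcomes with arm means set equal there.
- Name the adjusted arm difference at T2 as the main contrast.
- For each other scale, use its own T0 value as covariate.
- Make any latent growth curve secondary and piecewise, with knots at T1 and T2, so that the T0-T1 segment is separate.
- Optionally, add cohort as a fixed effect.

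The cost is wording only, since Table 2 already schedules the data. The main limitation is that T0 and T1 are pre-treatment but post-randomisation. Adjustment therefore leaves some recruitment imbalance in place, and the equal-means version assumes there is none. Report a sensitivity analysis that adjusts for T0 only.

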### Participants and recruitment

Approximately 8–12 adolescents of both genders are considered a preferred group size, and 30 groups will be recruited. The target population is students from the 1^st^ or 2^nd^ grade from upper secondary school, who are 16/17 years old. There is a maximum cut-off age of 20 years and subjects must have subclinical depression or mild to moderate depression, according to the criteria of the DSM. Inclusion will be evaluated through a semi-structured interview by the course instructor/control leader. Generally, the participants will be recruited through their general practitioner, the School Health Service, public health nurses, the Educational and Psychological Counselling Services (PPT) or the Children and Young People’s Psychiatric Out-patient Services (BUP). Exclusion criteria include presence of bipolar disorder, psychosis, substance-use, ADHD or ADD and brain damage as listed in the ACDC manual.

### Intervention: The “Adolescent Coping with Depression Course”

The “Adolescent Coping with Depression Course” (ACDC) is a CBT-based group course for adolescents with subclinical or mild to moderate depression developed for the Norwegian context [36]. The development was funded by the Norwegian Directorate of Health (HDIR). In the first effectiveness study [37] the intervention has demonstrated effect sizes of medium to large reductions in symptoms of depression. The reduction was maintained or even increased at follow-up six months later. It would be interesting to see whether this intervention can prevent dropout among upper secondary school students. The intervention also needs to be tested within an RCT design.

ACDC is based on a new and updated understanding of depression within CBT, and the program contains different approaches and methods taken primarily from the work of Rational Emotive Behaviour Therapy (REBT) [38] and Cognitive Behavioural Therapy (CBT) [39]. However, ACDC also includes elements from Meta-Cognitive Theory (MCT) [40] and Positive Psychology (PP) [41] in addition to modern neurobiological perspectives. Within Meta-Cognitive Theory the focus is on how to modify the experience and regulation of your own thoughts [40]. You learn how to reflect on your own thinking style within a meta-perspective, by being consciously aware of your thinking and how you can think about your own thoughts. It is also important to be aware of how thoughts can change in terms of quality and style, and how to deal with this. Positive psychology is used for breaking thinking patterns, on the basis of a neurobiological understanding of how thinking patterns, behaviour and emotions are formed and developed. Another important component in the course is affect regulation. Further, the neurobiological perspective is used to give adolescents a better understanding of how information is processed and why we react the way we do, sometimes automatically. With these conceptual understandings, the adolescents can root their work with the concrete techniques in a solid base. There is a focus on symptom relief within a systemic perspective, meaning family-school-workplace, and separate pamphlets are distributed to those.

The importance of practising the techniques learned on the course is emphasized both in and outside the course setting to develop the necessary skills. One of the goals of the course is for the adolescents to acquire a ‘toolbox’ of skills and techniques to help them cope better with their depressive symptoms in the future. The material includes a manual for the facilitator, a course pamphlet for the participants, a pamphlet addressed to parents and also a pamphlet for the school/workplace as well. Additionally, a short downloadable presentation has been developed for teachers to use in class to present mental health as a theme if required. All the course materials are printed and published by the Norwegian Council for Mental Health (NCMH).

The course is usually delivered in a group format over 8 consecutive weekly sessions, each lasting approximately 120 min, with breaks. If necessary, it could be delivered twice a week over a shorter period. Two follow-up sessions are conducted about 3 and 6 weeks after the last session, lasting approximately 90 min. In total, the ACDC consists of 10 sessions. Ideally, the sessions are at the same time every week and each session has a specified topic described above. Generally, the sessions start by summarizing the previous session and reviewing the homework assignments.

### Control group: Practice-as-usual group

The participants in the control condition will not be offered any intervention, but they will receive treatment as usual. This will involve standard treatments, including no treatment or the use of pharmacotherapy, that the active control course leaders typically employ. The participants as well as the control leader will be asked about what they give/receive as usual care to examine the practice-as-usual in detail.

### Measures

Table 2 presents the measures that will be administered at each measurement occasion.

#### Screening measure

Potential study participants will be screened for eligibility and provided with study information in a semi-structured interview. At the first meeting with the course instructors/control leaders, adolescents will be screened using the Beck Depression Inventory (BDI; [42]) and will have a brief clinical interview. BDI is a widely-used self-report measure of depression and assesses a wide range of depression symptoms. It consists of 21 items with four levels of severity for each symptom. The BDI is reported to be a reliable and valid measure for depressive symptoms in adolescents [43]. Adolescents who have a BDI score ≥ 10, and who are between 16 and 20 years old can be included in the study. If they agree to participate, written consent will be obtained and the first pretest will be filled in by adolescents at the end of the interview.

#### Primary outcome measures

Dropout will be measured from school reports.

The level of depressive symptoms as assessed by the Center for Epidemiologic Studies Depression Scale for adolescents (CES-D; [44]) will also serve as one of the primary study outcomes. CES-D asks for the frequency of symptoms during the last week of depressed affect (7 items), lack of positive affect (4 items), somatic and retarded activity (7 items), and interpersonal problems (2 items). A four-point Likert scale is used (total score range: 0–60). A previous confirmatory factor analysis supported the use of four dimensions invariantly to gender and differing ethnic backgrounds in Norway [45].

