Date of first enrolment	01/11/2015
Target sample size	35 clusters with 8–12 adolescents within each cluster
Recruitment status	Recruiting
Primary outcome(s)	1. Center for Epidemiological Studies Depression Scale, CES-D for adolescents, at Pre-test, T1, T2, T3, T4
	2. Dysfunctional Attitudes Scale (DAS) (short version) at Pre-test, T2, T3, T4
	3. Automatic Thoughts Questionnaire (ATQ) (short version) at Pre-test, T2, T3, T4
	4. Ruminative Response Scale (RRS) (short version) at Pre-test, T2, T3, T4
	5. Emotion regulation at Pre-test, T2, T3, T4
	6. Dropout (from school and official registries) at T1, T2, T3, T4
	7. Grades at T1, T2, T3, T4
Key secondary outcomes	1. Intentions to quit school at Pre-test, T2, T3, T4
	2. Social and Cognitive Competence at Pre-test, T2, T3, T4
	3. Life events at Pre-test, T2, T3, T4

Course leaders were recruited from the Educational Psychological Services, School mental health offices, and so on. To become certified as an ACDC course leader, one must have completed a minimum 3–year college/university education before attending the 5 day certification course. The trainers are either doctors, psychologists, nurses, educators, social workers, occupational therapists or physiotherapists. All are employed in community health, public health/public hospitals, schools or in private healthcare.

The course leaders have been randomized to experimental and control conditions by administrative personnel at the Norwegian Center for Child Behavioral Development. The control groups of adolescents will receive practice as usual, so those course leaders will be offered their training shortly after the experimental groups have finished after 14 weeks. Our design is thereby a cluster randomized trial where groups (course leaders) rather than individuals are randomized.

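### Dropout, a primary outcome, has two stated sources and no primary time point; no named model is said to suit it, and its detectable difference is large and unstated

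*Protocol article*

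**What the plan says.** Dropout is in the scientific title (Table 1), in the first research question (Aim of the study), and among the primary outcomes in two places.

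- **Primary outcome measures:** "Dropout will be measured from school reports".
- **Table 1, primary outcomes:** "6. Dropout (from school and official registries) at T1, T2, T3, T4".
- **Design:** a longer register follow-up is also planned: "Personal number will be kept for five years in order to collect relevant information from public registers to further examine dropout".

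No section defines the dropout event, says which source prevails if they differ, or names one of T1 to T4 as the primary time point.

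The Statistical analysis section names "repeated measures General linear models (GLM) for estimation of intervention effects" and adds multiple-group latent growth curves, with growth mixture models as an extension. It assigns no outcome to any method and does not mention the course-leader clusters.

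The power calculation treats depressive symptoms as the main outcome. It finds that, "with a .05 level of significance, power = .80, ICC = .08, number of clusters = 25, cluster size = 8" and N = 200, "we may be able to detect effect sizes of .49". No dropout rate by T4, target reduction or intraclass correlation (ICC) for dropout is given.

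**The concern.** Two analysts who follow the text could build different primary dropout variables from the same trial, one from school reports alone and one from school and register data, each at any of four time points. The text gives no rule for choosing between them.

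The named models also fit this outcome poorly. Participants are first- or second-year students at entry, so nobody has dropped out at the pretest, and T1 follows only one or two months later. The variable therefore starts at or near zero for everyone and takes values 0 or 1 afterwards. A repeated-measures model or growth curve across the waves does not directly answer how many more students had left by a given date in one arm than in the other. Neither model is said to allow for randomisation by course leader.

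Finally, the sample was sized on a continuous symptom score. If it can reveal only large reductions in dropout, a non-significant result at T4 says little on the question in the title, and a reader not told this may take it as evidence of no effect.

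**Working it through.** **Inputs from the article.** Significance level .05 (sidedness not stated; two-sided assumed), power .80, ICC .08 for depressive symptoms, 25 clusters of 8 (Sample size and power calculations). Allocation 1:1 by course leader: "Fifteen course leaders for the intervention group received their training for a full week in October 2015", with 15 more in the control arm (Design). Target of 35 clusters of 8–12 (Table 1). About one third of Norwegian students leave upper secondary school early (Background), the only population dropout rate given.

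**Assumptions.** Control-arm dropout by T4 of 10%, 15%, 20% or 33%. ICC for dropout from 0 to .08, the upper value borrowed from depressive symptoms.

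**1. The plan's own figure.** Design effect = 1 + (8 − 1) × .08 = 1.56. Detectable standardised difference = (1.960 + 0.842) × √(4 × 1.56 / 200) = 2.802 × 0.1766 = .495, against the stated .49. Power at .49 is 79%. The figure reproduces.

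**2. The same sample applied to dropout.** Effective n per arm is 100 at ICC 0 and 100 / 1.56 = 64.1 at ICC .08. For control rate p, intervention rate q and mean m = (p + q)/2,

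power = Φ{ [(p − q) − 1.96 √(2m(1 − m)/n)] / √[(p(1 − p) + q(1 − q))/n] }.

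Example: p = .333, q = .127, n = 64.1. The difference is .206, the null standard error .0744 and the alternative standard error .0721. Then (.206 − .146)/.0721 ≈ .84, so power is 80%.

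Solving for q at 80% power, N = 200 (relative reduction in brackets):

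| Control rate | ICC 0 | ICC .08 |
|---|---|---|
| 33% | 16.3% (51%) | 12.7% (62%) |
| 20% | 6.6% (67%) | 4.1% (80%) |
| 15% | 3.6% (76%) | 1.5% (90%) |
| 10% | 1.0% (90%) | 80% power not reached |

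For 33% against 25%, power is 25% at ICC 0 and 18% at ICC .08.

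**3. The 10% row.** Complete elimination (10% to 0%) at n = 64.1 gives z = .10 / √(.10 × .90 / 64.1) = 2.67. Since 2.67 − 1.96 = .71, power is about 76% (74% with the pooled formula above). With 30 groups of 8, n = 120 / 1.56 = 76.9, z = 2.92 and power is about 83% (82% pooled). Normal approximations are rough at a rate of zero.

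**4. The largest target.** 35 × 12 = 420, with design effect 1 + 11 × .08 = 1.88 at ICC .08. From 33%, dropout must fall to 21.2% (36%) at ICC 0 or 17.1% (49%) at ICC .08. From 15% the reduction needed is 56–73%; from 10% it is 68–86%.

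**5. Clustering.** If the ICC for dropout were .08 and the clusters were ignored, the standard error would be too small by a factor of √1.56 = 1.25.

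**The case against.** The strongest reply is that this is a condensed article. The Statistical analysis section ties no outcome to a model, latent growth curves can be fitted to categorical data, and a separate analysis plan may assign a suitable method to dropout. That stands. A reader might infer that dropout will be analysed by a normal-theory model with invalid standard errors and no interpretable effect. The article does not say so, and a linear model on 0/1 data still estimates a risk difference. What remains is narrower: the article chose to name its effect models, and none is said to suit a binary outcome or the clusters.

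School and register data may complement each other. That is possible, but the two statements still differ and no order of precedence is given. A reader might go further and treat dropout as irreversible, or assume that a student who changes school counts as a leaver in one source and as enrolled in the other. The article says nothing on returning students or on how either source is coded, so neither claim is supported.

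The article claims no power for dropout, and its Discussion speaks only of possibly preventing it. The Design section already plans register follow-up beyond T4, so T4 is not the only horizon. Both points stand. They do not remove dropout from the primary outcomes or fix its time point.

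Every dropout rate and ICC used here is assumed. Depressed students may leave school more often than the general third; at a 50% rate and N = 200 the reduction needed is 39–48%.

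**Conclusion.** The point holds in this form: a primary outcome has two differing source statements and no primary time point, and no named effect model is said to handle a binary outcome or the randomised clusters. The difference in sources is in the published text and would need reconciling whatever a separate analysis plan says.

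On size, at the N of 200 used for power, the detectable relative reduction is 51–62% at a one-third dropout rate and 76–90% at 15%. At the largest stated target it is 36–49% at one third. These figures rest on a two-sided .05 test, 80% power, an ICC of 0 to .08 and assumed T4 rates. The one-third figure is not a T4 rate: T1 to T4 runs from January 2016 to June 2017 in the first cohort. The final sample is also open, since 19 of 30 groups were established in that cohort and a second is planned.

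A reader might conclude that a 10% rate makes even complete elimination undetectable. It does not: power is about 76% at ICC .08, and about 83% with 30 groups of 8. Nor do the documents require that dropout be made secondary or that the five-year register analysis become the definitive one. Those are trade-offs for the sponsor, not corrections.

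**What to change.** 1. Reconcile Table 1 and the Primary outcome measures section to one definition and one source, for example register-recorded as not enrolled and not completed, with school reports as a check. State how students who change school or return are counted.
2. Name one primary time point, such as T4, and describe the later register follow-up as a separate analysis.
3. Analyse dropout once at that time point, with a logistic mixed model or generalised estimating equations clustered on course leader and a small-sample correction. Report the risk difference and its 95% confidence interval.
4. State that the power calculation covers depressive symptoms only, and give dropout's detectable difference under stated rates and ICCs, as in the table above.
5. State that a non-significant result at T4 will be reported with its interval and not as evidence of no effect.

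The cost is small: definition wording and a little more analysis. Register access is already planned, so no new data collection is needed.
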